#### Primary target parameter

The primary aim is to investigate changes in hospitalization rates of cancer patients.

The underlying hypothesis is that participation in the cancer patient navigation program is able to reduce the number of patients who need to be re-hospitalized within 12 months. The hospitalization rate (defined as at least one night spent in hospital within a 12-month follow-up period) is estimated to be 25% in the control group and 12.5% in the intervention group.

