## Methods/design

In line with the primary study objective, the design was chosen so that evidence of the effectiveness of the intervention can be generated at the highest possible level of evidence. The project was therefore designed as a prospective randomized, longitudinal, multicenter study. To our knowledge, no other RCT has been conducted in Germany on this topic. Other groups used a quasi-experimental design in which the control group was generated from insurance data [11]. A multicenter approach was chosen to obtain larger sample sizes and to ensure that the study optimally represents cancer centers. In addition, various types of cancer will be considered to assess the effectiveness of the program across multiple indications.

The program was implemented at five centers in Saxony, Germany. The evaluation also takes into account the network partners (office-based physicians) of the specialized hospitals, insofar as they contribute patients to the program.

Eligible patients are identified during their hospitalization in the participating centers and are informed about the study in a personal interview and with the help of written documents. If the patients give their written consent, they are randomized to the intervention group or the control group on a one-to-one basis. They are randomized with regard to the center, the type of cancer, gender, and age group. The following cancers are documented: pancreatic, gastric, colonic/rectal carcinoma, gynecological cancer and melanoma. While patients in the control group receive standard care, those in the intervention group are also in regular contact with their patient navigator.

The observation period in the intervention (cancer patient navigation program participation) and control (no cancer patient navigation program participation) groups is 12 months per patient. In this time period about 20 talks with the cancer patient navigation program specialists shall be held.

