### Statistics

#### Sample size planning

The sample size planning is based on the primary endpoint, whose one-year incidence is estimated to be 25% in 2015 and 2016 according to data from the participating study centers. Based on earlier study findings, the case management program can halve the number of hospitalizations [11].

Thus, a hospitalization rate of 12.5% is expected in the intervention group. To illustrate this difference at a significance level of alpha = 5% and a statistical power of 80%, 152 patients per group are needed (chi^2^ test, normal approximation, PROC POWER SAS 9.4). Taking into account a dropout rate of 10% during the 12-month study period, a total of 170 patients per group, or 340 patients in total, are needed at baseline.

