#### Primary endpoint

As a starting point, the hospitalization rates, defined as the percentage of patients who spend at least one night in hospital during the one-year study period in the two groups, are compared by means of the chi^2^ test. The results are verified in a second analytical step using a general linear model that takes into account other influencing factors.

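### The lead test of the primary endpoint leaves out the four factors used in randomization, and the adjusted second step names a model class for continuous outcomes

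*Protocol article*

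**What the plan says.** All references are to the protocol article.

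- **Methods/design** sets 1:1 allocation and then names the factors that randomization takes into account: "They are randomized with regard to the center, the type of cancer, gender, and age group".
- **Statistics, Primary endpoint** makes the outcome binary per patient. The rate is "defined as the percentage of patients who spend at least one night in hospital during the one-year study period", and the two rates "are compared by means of the chi^2^ test". The article presents this test as the starting point. The second step reads: "The results are verified in a second analytical step using a general linear model that takes into account other influencing factors".
- **Primary target parameter** gives the planning rates. Hospitalization "is estimated to be 25% in the control group and 12.5% in the intervention group".
- **Sample size planning** is built on the same unadjusted chi-square test: "at a significance level of alpha = 5% and a statistical power of 80%, 152 patients per group are needed". Allowing for 10% dropout, the article arrives at 170 per group, 340 in total.
- **Other secondary and explorative endpoints** refers further analyses to a statistical analysis plan, which is not at hand.

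**The concern.** Two stated choices do not fit together well.

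First, the design takes trouble to balance four factors, and the lead test then uses none of them. Balancing a prognostic factor reduces the true variability of the difference between arms. An unadjusted test does not see that reduction and keeps using the larger total variance. Its p-value is then too cautious, and precision bought by the design goes unused. Eligible cancers range from melanoma to pancreatic cancer and stages run from 0 to IV, so differing hospitalization risks across the randomization factors are plausible, though the article gives no figures.

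Second, the model in the verifying step is named as a general linear model, which is meant for a continuous outcome with constant variance. The endpoint is yes/no. An analyst cannot tell whether linear or logistic regression is intended. A literal reading yields no odds ratio and fitted risks that are not confined to 0–1.

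**Working it through.** **1. The plan's own figure.** Inputs from the article: p₁ = 0.25, p₂ = 0.125, alpha 5% (taken as two-sided), power 80%. The mean rate is 0.1875.

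n = [1.960·√(2·0.1875·0.8125) + 0.842·√(0.25·0.75 + 0.125·0.875)]² / 0.125²
= [1.960·0.5520 + 0.842·0.5449]² / 0.015625 ≈ 151.9, so **152 per group**, as stated.

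Power at 152 per group is 80.0%. Dropout: 152/0.90 = 168.9, so 169 against the stated 170, which is immaterial.

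**2. Why the unadjusted test can be conservative.** The chi-square test uses the total variance p̄(1 − p̄). When arms are balanced within strata with risks pₛ, the difference between arms varies only with the average of pₛ(1 − pₛ). The excess is p̄(1 − p̄) − mean[pₛ(1 − pₛ)] = Var(pₛ). It is zero if the factors are not prognostic and positive otherwise.

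**3. Size, by simulation.** Assumptions, because the article gives neither the prognostic strength nor the allocation algorithm: 304 patients, 20 strata, permuted blocks of 4 within strata, and between-stratum SD on the logit scale of 0, 0.5, 1.0 or 1.5. Overall rates were held at 25% vs 12.5% for power and at 25% in both arms for type I error. There were 5,000 runs per scenario. To show what each SD means, the second column gives the odds ratio between a stratum 1 SD above and one 1 SD below the mean, exp(2·SD). CMH is the Cochran-Mantel-Haenszel test on the strata.

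| SD | Odds ratio, ±1 SD | Type I, chi-square | Type I, CMH | Power, chi-square | Power, CMH | Points forgone |
|---|---|---|---|---|---|---|
| 0 | 1.0 | 5.7% | 5.5% | 81.1% | 80.7% | −0.4 |
| 0.5 | 2.7 | 4.6% | 5.0% | 81.2% | 81.9% | 0.7 |
| 1.0 | 7.4 | 3.8% | 5.4% | 82.1% | 85.2% | 3.1 |
| 1.5 | 20.1 | 2.4% | 4.8% | 84.0% | 89.5% | 5.5 |

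The Monte Carlo standard error for type I error is √(0.05·0.95/5000) ≈ 0.3 points, so the SD 0.5 row is barely distinguishable from no effect. With a 12.5% rate in both arms the chi-square type I error is 4.7%, 4.2%, 4.0% and 3.3%, which is the same pattern but milder.

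**4. The linear model.** The arm variances are 0.25·0.75 = 0.1875 and 0.125·0.875 = 0.1094, a ratio of 1.7. With equal arms, the pooled-residual standard error of the risk difference is √[((0.1875 + 0.1094)/2)·(2/152)] = 0.0442. The unpooled binomial standard error is √[0.1875/152 + 0.1094/152] = 0.0442, the same value. In the simulation the stratum-adjusted linear model had type I error 4.4–5.5% and power 80.8–89.5%, in line with CMH. Robust standard errors made no material difference.

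**5. How much adjustment the data can carry.** Expected events: 304 × 0.1875 = 57. With 5 centers, 5 cancer types, gender and an assumed 2 age groups, main effects need 4 + 4 + 1 + 1 = 10 terms plus treatment, so 57/11 ≈ 5 events per parameter. Full cross-classification would give 5·5·2·2 = 100 cells for 340 patients.

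**The case against.** The strongest defence is that the plan is coherent as it stands. The trial is powered on the chi-square test, the sample size reproduces exactly, and an unadjusted test after balanced randomization remains valid. Where it errs, it errs on the safe side. An adjusted second step is already planned, and nothing excludes the randomization factors from it. The word general may be a slip for generalized. The gain from adjustment rests on assumed prognostic strength and is below one point in the weakest prognostic scenario.

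Most of this stands and limits the point. A reader might go further in four ways that the document does not support:

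- *The trial is underpowered or the sample size is wrong.* It is not. Power is forgone relative to a better test, and there is no shortfall below 80%.
- *False positives are inflated.* The error runs in the opposite direction.
- *The linear model gives wrong standard errors because the arm variances differ by a factor of 1.7.* With 1:1 allocation the pooled and unpooled standard errors coincide at the planned rates.
- *Two primary results compete, with unnamed covariates and no rule for disagreement.* The article orders the steps and powers the trial on the first. The covariate list and a disagreement rule can properly sit in the analysis plan that is not shown.

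The defence does not remove the stated choice of lead test or the stated model class. Both are fixed in this article, and both can be improved without cost to the design.

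**Conclusion.** The point holds as a recommendation on efficiency and wording. The lead test does not use the factors on which the patients were randomized. If those factors predict hospitalization, the test is conservative (type I error about 2.4–4.6% at a 25% rate) and forgoes about 1 to 5.5 power points. The upper end requires very strong prognosis. These figures depend on the assumed between-stratum SDs, the assumed 20 strata and the assumed block allocation. With non-prognostic factors the loss is nil. The model name is wrong for a yes/no endpoint and should be corrected, but a literal linear model would not materially distort the treatment test here.

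**What to change.** Name one adjusted analysis as primary, correct the model name, and keep the unadjusted chi-square as supportive. Suggested content:

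> The primary comparison of 12-month hospitalization uses logistic regression (a generalized linear model) with treatment and main effects for center, cancer type, gender and age group. Sparse levels are merged by a rule fixed without reference to outcomes by arm. The result is reported as a standardized risk difference with 95% confidence interval. The unadjusted chi-square test is supportive.

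The standardized risk difference keeps the result on the scale used for planning. A CMH test on a few merged strata is an alternative. CMH by cancer type alone is not equivalent, because it leaves out center, gender and age group. Full cross-classification should be avoided.

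The cost is a change of wording and slightly more analysis work, together with the discipline of limiting the number of terms to what about 57 events can support. No further patients are needed, and the factors are already used in randomization. The article describes the study as ongoing, so the change should be dated and made before outcomes by arm are seen.

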#### Secondary endpoint

The differences in the HADS-S score between the intervention group and the control group are compared by means of the T test, and changes over time by means of an analysis of variance (ANOVA).

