**Methods:**

The study population in this evaluation comprises cancer patients with gastric carcinoma, pancreatic carcinoma, colorectal cancer, melanoma or gynecological cancer who have been hospitalized at least once at one of the study centers as well as their relatives, outpatient and inpatient physicians, and cancer nurses. It is planned to randomize 340 cancer patients (stomach, colonic/rectal cancer, gynecological cancer, melanoma) at five centers to an intervention group (care by patient navigators based on standardized operating procedures) or a control group in a one-to-one ratio. The primary target parameter is the number of hospitalizations within the 12-month intervention period. The participants are asked to complete various questionnaires on patient-related outcomes at baseline and at 3 and 12 months (SF 36, HADS, PAM 13, and others). Data on drug therapy, utilization of health services, and medical expenses will also be analyzed.

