#### Secondary target parameter

The secondary target parameter is whether the control group and the intervention group differ in their HADS-D scores as a surrogate of psychological stress.

The underlying hypothesis is that the patients’ psychological burden is reduced by participation in the patient navigation project. Patients in the intervention group will have a lower level of anxiety and stress on the HADS-D scale compared to baseline (t1) and will have a lower level at three and 12 months compared to the control group.

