#### Statistical methods

The data are analyzed using SAS Version 9.4 (SAS Institute Inc., Cary, NY, USA). In general, the data analyses focus on the differences between the intervention group and the control group at baseline and the other data-collection times in the study. An error probability of alpha = 0.05 is defined as the significance level.

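### The between-arm HADS t test leaves out the baseline HADS score already collected, and the hypothesis counts a within-arm fall from baseline as evidence of effect

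*Protocol article*

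**What the plan says.** All references are to the protocol article.

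- **Secondary endpoint (statistics).** "The differences in the HADS-S score between the intervention group and the control group are compared by means of the T test". The sentence goes on to assess "changes over time by means of an analysis of variance (ANOVA"). No covariate is named for the t test. The factors of the ANOVA, its use of t1 and any arm-by-time term are not given.
- **Secondary target parameter.** The hypothesis has two parts. The first is within one arm: "Patients in the intervention group will have a lower level of anxiety and stress on the HADS-D scale compared to baseline (t1"). The second is between arms: intervention patients "will have a lower level at three and 12 months compared to the control group".
- **Abstract, Methods.** Patients fill in "questionnaires on patient-related outcomes at baseline and at 3 and 12 months (SF 36, HADS, PAM 13, and others"), so a baseline HADS is planned for every patient. Methods/design places t1 during the hospital stay, t2 at three months and t3 at twelve.
- **Statistical methods.** Analyses centre on "differences between the intervention group and the control group at baseline and the other data-collection times in the study", with alpha of 0.05.
- **Methods/design, on allocation.** "They are randomized with regard to the center, the type of cancer, gender, and age group". Baseline HADS is not among these factors.
- **Primary endpoint (statistics).** A second, adjusted model is planned for hospitalization. None is stated for HADS.

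**The concern.** Baseline HADS is likely to predict follow-up HADS. A between-arm test that omits it carries variance that could be removed at no cost. It also leaves any chance baseline difference between the arms in the estimate, and the design does not balance on HADS. The trial is sized for hospitalization and states no power for HADS, so lost precision has no planned reserve behind it.

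The within-arm clause raises a separate issue. Distress measured during a cancer admission may ease afterwards in both arms. A fall from t1 in the intervention arm alone does not separate navigation from recovery or regression to the mean, which is why there is a control arm. If the clause stays in the hypothesis, such a fall could be reported as partial confirmation.

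Two smaller points bear on the same endpoint. The hypothesis names two visits without saying whether both must succeed. The score is called HADS-D in the hypothesis and HADS-S in the analysis section.

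**Working it through.** **The plan's own figure.** The only sample size given is for hospitalization: 25% against 12.5%, alpha 5%, power 80%. With the pooled rate 0.1875 under the null, two-sided:

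n = [1.960·√(2·0.1875·0.8125) + 0.842·√(0.25·0.75 + 0.125·0.875)]² / 0.125² = 151.9, so 152 per group, as stated. Dividing by 0.9 gives 168.9, so 169 against the stated 170. This figure is not in dispute. I use 152 per arm below.

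**Assumed inputs.** The article gives no SD, target difference or baseline correlation for HADS. I assume a true difference of 0.3 SD and a baseline-to-follow-up correlation r of 0.4 to 0.7.

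**Formulas (normal approximation, SD = 1).** Power = Φ(0.3/√(2V/152) − 1.96), where V is

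- 1 for the t test on follow-up scores;
- 1 − r² for baseline-adjusted ANCOVA;
- 2(1 − r) for a between-arm comparison of change scores, which is one possible reading of the ANOVA.

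For the t test, √(2/152) = 0.1147 and 0.3/0.1147 = 2.615, so power = Φ(0.655) = 74%.

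| r | ANCOVA variance | t test power | ANCOVA power | Change-score power |
|---|---|---|---|---|
| 0.4 | 84% | 74% | 81% | 67% |
| 0.5 | 75% | 74% | 86% | 74% |
| 0.6 | 64% | 74% | 90% | 83% |
| 0.7 | 51% | 74% | 96% | 92% |

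In sample-size terms, ANCOVA at r = 0.5 is worth an unadjusted trial of 152/0.75 ≈ 203 per arm.

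**Chance imbalance.** The standard error of the baseline HADS difference is √(2/152) = 0.115 SD.

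**Within-arm clause.** Suppose navigation has no effect and HADS falls by 0.2 SD in both arms after the admission (assumed). The standard error of the mean change in one arm of 152 is √(2(1 − r)/152). The chance of a significant fall is 1 − Φ(1.96 − 0.2/SE):

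- r = 0.5: SE = 0.0811, chance 69%;
- r = 0.7: SE = 0.0628, chance 89%.

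**Two visits, each tested at 0.05.** With a correlation of 0.5 to 0.6 between the two test statistics and no effect at either visit, the chance that at least one is significant is about 9%. The chance that both are is about 1%.

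**The case against.** **The test is not wrong.** Under randomization the unadjusted t test is unbiased and keeps its type I error. This stands: the loss is precision and exposure to chance imbalance.

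**The plan may use the baseline elsewhere.** A reader might infer that the HADS analysis ignores t1 altogether. The text does not support that, because an analysis of change over visits t1 to t3 most naturally starts at t1. If the ANOVA compares change between arms, the shortfall against ANCOVA shrinks to about 7 points at r = 0.6 and 3 points at r = 0.7. At r = 0.4 and 0.5 change scores do no better than the t test, so the full gap remains there. The article does not state the contrast, and an article may leave such detail to the SAP. It does, however, fix the t test itself.

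**The false-positive rate is not established as inflated.** A reader might infer a 9% risk from the two visits. That holds only if success at either visit is enough. The hypothesis can equally be read as requiring both, and then the risk does not exceed 5%.

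**The within-arm clause is paired with a valid comparison.** The planned t test is between arms, and Statistical methods focuses on arm differences. No within-arm test is explicitly planned as proof of effect. So this is a minor flaw in the wording of the hypothesis.

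**Missing HADS data are not ignored.** A reader might infer that incomplete visits go unaddressed. Handling of missing values provides questionnaire-specific rules, analyses of patients with incomplete records, and a conditional LOCF analysis. Nor would a mixed model by itself settle how deaths are treated, since there is no HADS score after death.

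**Conclusion.** The point holds as a free improvement, not as an error that invalidates the analysis. The protocol fixes an unadjusted between-arm t test for HADS although baseline HADS is collected. Against ANCOVA this costs about 7 to 21 percentage points of power (74% against 81% to 96%), given an assumed 0.3 SD difference, 152 per arm and r of 0.4 to 0.7. The loss is smaller at the upper correlations if the ANOVA compares change scores between arms. None of these HADS inputs comes from the document, so the range is illustrative, although any non-zero r favours adjustment. The within-arm fall from t1 cannot show an effect of navigation and does not belong in the hypothesis. The success rule across the two visits and the HADS label need to be stated clearly.

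**What to change.** 1. Replace the t test with ANCOVA, or with a mixed model for repeated measures on the 3- and 12-month HADS. Include baseline HADS, arm, visit, arm-by-visit and the randomization factors (center, cancer type, gender, age group). For ANCOVA at a single visit, the visit terms drop out.
2. State the hypothesis as a between-arm difference only, and report within-arm change from t1 descriptively.
3. Say whether success needs a difference at both visits or at one named lead visit, with the other supportive.
4. Reconcile HADS-S and HADS-D so that the score tested is clear.

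The cost is analysis wording only. Baseline HADS is already collected, and no visit, patient or questionnaire is added.

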#### Other secondary and explorative endpoints

Subgroup analyses are planned, especially in respect of the cancer type (indication), the cancer state, the cancer relapse status, and the presence of metastases.

In the addition, the following subgroups are evaluated:Patients in employment immediately after the cancer diagnosisPatients in employment after the first treatment, at the start of rehabilitationPatients of retirement age immediately after the cancer diagnosisPatients of retirement age after the first treatment, at the start of rehabilitation

Other analyses and possibly tests for statistical significance are specified in the statistical analysis plan.

#### Handling of missing values

Missing values and premature withdrawals are documented. Detailed analyses are conducted of patients with incomplete data records.

The method for handling missing values depends on the standard specifications of the individual questionnaires. They differ, for example, in the number of permissible data items missing and in the method for replacing any missing data.

Two predefined intent-to-treat (ITT) populations are used for analyzing the primary endpoint:ITT-1: All patients who were randomized to one of the two treatment groups. If a patient dies before the end of the study, the actual hospitalization rate is used for the primary endpoint.ITT-2: All patients who were randomized to one of the two treatment groups. If a patient dies before the end of the study, the patient is regarded as hospitalized for the primary endpoint.PP: All patients for whom data are available at the time of the evaluation.

If the number of prematurely withdrawn patients differs significantly from the expected 10% limit, additional sensitivity analyses will be performed. In this case, a last-observation-carried-forward (LOCF) analysis is planned.

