#### Number of hospitalizations (primary endpoint)

This information is obtained by surveying the patients and also provided by the participating centers (medical controlling). Hospitalization is defined as a hospital stay which includes at least one overnight stay any time after the start of the study.

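### LOCF, the only named sensitivity method for withdrawals, would treat leavers without a recorded admission as admission-free to month 12, and its 10% trigger ignores imbalance between arms

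*Protocol article*

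**What the plan says.** The primary endpoint (Primary endpoint) compares hospitalization rates, "defined as the percentage of patients who spend at least one night in hospital during the one-year study period in the two groups". It is therefore a cumulative yes/no outcome over 12 months. On its source, Number of hospitalizations (primary endpoint) says: "This information is obtained by surveying the patients and also provided by the participating centers (medical controlling"). Under Methods/design, patients are surveyed in hospital, at three months and at twelve months.

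Handling of missing values defines two intent-to-treat sets and a per-protocol set for this endpoint. The two intent-to-treat sets differ only in how deaths are counted. Neither says how a living patient who withdraws is coded. The section then sets a trigger, "If the number of prematurely withdrawn patients differs significantly from the expected 10% limit, additional sensitivity analyses will be performed", and a method, "In this case, a last-observation-carried-forward (LOCF) analysis is planned". It names neither the test behind the trigger nor the endpoint to which LOCF applies, and it gives no criterion by arm.

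**The concern.** A patient's status on this endpoint can only move from no to yes. Carrying the last value forward keeps every yes and freezes every no, so it assumes zero admissions after exit. On survey data the last value before month 12 dates from month 3 at the latest, which can leave nine months of risk uncounted. The error always understates the risk. How it affects the comparison depends on which arm loses more patients.

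Unequal loss is plausible, because only the intervention arm has about 20 talks with a navigator (Methods/design). The trigger nevertheless looks at one pooled number. A marked imbalance can pass unnoticed, and when the trigger does fire, the method it calls is itself sensitive to the imbalance. At stake is whether the sensitivity analysis can support or challenge the primary result.

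**Working it through.** **Inputs from the protocol article.** The 12-month rate "is estimated to be 25% in the control group and 12.5% in the intervention group" (Primary target parameter). Allocation: "they are randomized to the intervention group or the control group on a one-to-one basis" (Methods/design). Sample size planning: "at a significance level of alpha = 5% and a statistical power of 80%, 152 patients per group are needed", raised to 170 per group for 10% dropout.

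**The plan's own figure.** A two-sided chi-square test with pooled variance and no continuity correction gives 152 per group for 25% versus 12.5% (power 80.0%). Then 152/0.9 = 168.9, or 169, against the stated 170. The figure reproduces. With all 170 per group observed, power is 84%.

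**Trigger.** Take 9 control and 25 intervention withdrawals out of 170 each (5.3% and 14.7%).
- Total: 34/340 = 10.0%, so no test against 10% can fire.
- Between arms: difference 16/170 = 0.0941; SE = √(0.1 × 0.9 × 2/170) = 0.0325; chi-square = (0.0941/0.0325)² = 8.37; p = 0.004.

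If the unnamed test is an exact two-sided binomial test (an assumption), it fires at 23 or fewer (p = 0.046) or 46 or more (p = 0.037) of 340.

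**LOCF rate.** With withdrawal share d and true 12-month risk p, the LOCF rate is p(1 − d) + d·q, where q is the share of leavers with an admission recorded before exit. Withdrawal by arm, exit timing and constant hazard are assumptions; the article gives none of them. With λ = −ln(1 − p):
- exit before any admission is recorded: q = 0;
- exit at month 3: q = 1 − (1 − p)^0.25 = 6.9% for p = 25%, 3.3% for p = 12.5%;
- exit uniform over the year: q = 1 − p/λ = 13.1% and 6.4%.

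LOCF thus counts between none and about half of the leavers' true risk.

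**Power or rejection rate.** Φ((Δ − 1.96·SE0)/SE1) at 170 per arm, with SE0 pooled and SE1 unpooled; under no effect both tails are added. Example, planned effect, 20% control and 10% intervention leaving at month 3:
- control 0.8 × 0.25 + 0.2 × 0.0694 = 21.4%;
- intervention 0.9 × 0.125 + 0.1 × 0.0328 = 11.6%;
- Δ = 9.8 points, SE0 = 0.0402, SE1 = 0.0399, power 69%.

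| Scenario (control / intervention withdrawal) | Exit before any admission | Month 3 | Uniform |
|---|---|---|---|
| No effect, 10% / 30%: spurious benefit (points) | 5.0 | 3.6 | 2.4 |
| Same: two-sided rejection rate | 21% | 13% | 8% |
| Planned effect, 20% / 10%: power | 60% | 69% | 75% |
| Planned effect, 10% / 20%: power | 88% | 87% | 86% |

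These scenarios have 68 (10%/30%) or 51 (20%/10% and its reverse) withdrawals in total, so the trigger would fire under the exact test.

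**Comparator.** Part of any power loss comes from losing patients, not from LOCF. Complete cases with 20% / 10% loss leave 0.8 × 170 = 136 and 0.9 × 170 = 153 patients. At unbiased rates of 25% and 12.5%, power is 78%.

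**The case against.** Several points on the other side stand.

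- **Not every leaver becomes a no.** A reader might infer that LOCF codes all early leavers as never hospitalized. It does not, because an admission recorded before exit is kept.
- **The endpoint is inferred.** The section also deals with questionnaires collected at three time points, where LOCF is a more usual choice. Its position directly after the primary-endpoint populations makes the primary endpoint the likelier reading, but the text does not say so.
- **It is not shown to be the only protection.** The section also promises documentation of withdrawals and detailed analyses of incomplete records, speaks of sensitivity analyses in the plural, and defines a per-protocol set. The statistical analysis plan, not shown, may add methods. LOCF is the only sensitivity method named, and it is not the primary analysis.
- **The trigger's test is not named.** The cut-offs of 23 and 46 rest on an assumed exact test. The 9 versus 25 example does not, since the total is exactly 10%. That the rule could also fire on low withdrawal matters little; an extra analysis then does no harm.
- **The size depends on assumptions.** With equal withdrawal and no true effect, LOCF leaves the rejection rate at 5%. Under the planned effect the direction changes with the imbalance.

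None of this makes LOCF suitable for a cumulative endpoint, or makes a pooled count sensitive to a difference between arms.

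**Conclusion.** The point holds as a flaw in a stated rule, on condition that LOCF is meant for the primary endpoint. LOCF then understates the hospitalization risk and biases the comparison whenever withdrawal differs by arm; the trigger does not look for that difference. The two faults act in different situations: when the trigger stays silent, LOCF is not run and the article states no other rule for living withdrawals; when it fires, the analysis that follows can mislead.

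Under the assumptions above, LOCF can create a spurious benefit of 2.4 to 5.0 points with a rejection rate of 8% to 21% (10% control versus 30% intervention withdrawal). It can lower power to 60% to 75%, against 78% for complete cases (20% versus 10%), or raise it to 86% to 88% (10% versus 20%). A reader might infer a bias in one fixed direction between the arms, or charge the whole fall from 84% to LOCF. The documents support neither: they give no withdrawal by arm, and part of the fall is due to losing patients. The principle is secure; the figures are illustrations.

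**What to change.** For the primary endpoint, delete LOCF and the 10% trigger. Report withdrawal by arm, and always run one arm-aware sensitivity analysis, such as multiple imputation by arm with a tipping-point analysis.

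For patients who stop answering questionnaires, use the centers' medical-controlling data to month 12 where consent allows, and note that admissions at non-participating hospitals may be missed. Add a time-to-first-admission analysis censored at withdrawal only if admission dates are available. The article does not say that they are; Utilization of healthcare services lists duration and reason of hospital stays, not dates.

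The cost is a change of analysis wording and some extra programming and analysis work, with no new visits. As the article describes the study as ongoing, the change should be fixed before outcomes are analyzed by arm.
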